## Methods

### Project design

#### QUICK - II consist of two consecutive parts

In *part 1 *of the study, we will develop a stakeholder based Cardiovascular Health Education Program (CHEP) that is to be used to educate patients at risk of CVD who are enrolled in a private health insurance plan in rural Nigeria. To develop CHEP, we will use the following step-wise approach: (i) open qualitative interviews will be conducted with key stakeholders in CVD care to explore their perceptions on CVD, CVD risk factor management and CVD prevention and care. These stakeholders include patients at risks for CVD, healthcare providers (HCP), and health insurance managers of HCHP; (ii) on the basis of the outcomes of interviews with patients, CHEP will be developed; (iii) supportive strategies needed to implement CHEP successfully will be identified on the basis of the outcomes of the interviews with HCP and health insurance managers.

In *Part 2 *of the study we aim to evaluate the effect of CHEP through a prospective hospital-based study, using a pre-post intervention design. Measurements will be conducted in a subset of patients included in QUICK - I: those who have uncontrolled hypertension or other CVD risk factors, or are non adherent to medication after 12 months of treatment.

In addition, case file data will be reviewed and interviews with health care professionals in the participating clinic will be held and analyzed to evaluate the feasibility of the application of CHEP in practice.

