### Outcomes

The primary outcome of the evaluation of CHEP will be the changes in adherence to medication or life style recommendations. This will be assessed through the Morisky self-report medication adherence questionnaire [14]. This scale asks patients to respond yes or no to five questions. Each positive answer is assigned a score of one, with higher scores indicating poorer adherence. The same scale will be used for other life style recommendations (e.g. salt intake). As such, self-reported adherence will be assessed as a continuous measure.

Secondary outcomes are changes in physiological measures - systolic blood pressure, diastolic blood pressure, and body mass index (BMI) or abdominal obesity at 6 months after baseline.

Table 2 indicates definitions of what we consider as significant improvement per outcome measure.

**Table 2 T2:** Definitions of significant improvement per outcome measure

Outcomes	Significant improvement
Adherence to medication and life style recommendations (Primary outcomes)	Using the distribution on the Morisky scale [14] of low, medium, and high adherence ratios, a post CHEP effect shift of 10% to a higher category will be defined as a significant improvement in adherence.

Blood pressure (Secondary outcome)	Blood pressure decrease of >10% systolic or diastolic or blood pressure at target level (patients without diabetes or established CVD: <140 mmHg systolic and <90 mmHg diastolic, patients with diabetes, renal disease or established CVD: <130 mm Hg systolic and <80 mmHg diastolic).

Body mass index (kg/m^2 ^)	No CVD risk: <25 Moderate CVD risk: 25-30 High CVD risk: >30 In patients with a BMI >25 any reduction of BMI at 6 months will be regarded as an improvement.

Data will also be collected about other factors that may influence patients' hypertension management: self-reported cardiovascular risk factors (physical activity, diet, smoking, alcohol, sodium intake), knowledge of HTN and HTN management, perceptions of HTN, perceptions of medications, self efficacy, experienced stress, patient satisfaction with care (e.g. doctors' performance, supply of medication, frequency of follow up, satisfaction with CHEP etc).

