### Data Analysis

#### Statistical methods

The rate of adherence will be examined according to the intention to treat principle. Primary and secondary outcome measures will be calculated for every patient at baseline and 6 months thereafter to assess possible improvements. Furthermore, univariate and multi-level analyses will be performed to evaluate the modifying effect of the outcome measures (see above) on adherence or blood pressure. If the N is sufficient, we will perform separate subgroup analyses for gender. While a *p *value of 0.05 will be the critical value for all analysis, the *p *value will be adjusted for subgroup analysis according to standard procedures.

Data from interviews with HCP will be analyzed and used to identify potential barriers to the implementation of CHEP in practice.

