The design of our evaluation of CHEP could have been improved by using a control group and a randomized design. However, the study is conducted in a very specific context, where it is impossible to avoid contamination. For example, patients have generally long waiting hours and may communicate about their condition or the treatment with each other. Moreover, the number of health care professionals in the clinic is limited such that it would be impossible to randomize them into a control and experimental condition. In addition, given the context of the community health insurance program, other clinics that provide standard cardiovascular care are difficult to find in the region. Nevertheless, to address this limitation, we consider analyzing the data collected during QUICK - I study for the patients included in QUICK - II to further compare and evaluate the effects of CHEP.

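### Table 2 judges blood pressure by a per-patient responder rule that has no baseline value and no reference rate in a one-group study; the conclusion should rest on the paired mmHg changes already named as outcomes

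*Protocol article*

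**What the plan says.** The Outcomes section of Part 2 states: "Secondary outcomes are changes in physiological measures - systolic blood pressure, diastolic blood pressure, and body mass index (BMI) or abdominal obesity", assessed at 6 months. These are continuous measures.

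It then says: "Table 2 indicates definitions of what we consider as significant improvement per outcome measure". For blood pressure the table gives "Blood pressure decrease of >10% systolic or diastolic or blood pressure at target level". The target depends on the patient: one level for patients without diabetes or established CVD, and for others "patients with diabetes, renal disease or established CVD: <130 mm Hg systolic and <80 mmHg diastolic".

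Statistical methods adds: "Primary and secondary outcome measures will be calculated for every patient at baseline and 6 months thereafter to assess possible improvements". It sets 0.05 as the critical p value for all analyses. It does not say whether the Table 2 class or the mmHg change is the quantity tested.

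Part 2 evaluates the programme "using a pre-post intervention design", in one group, with assessments at baseline and 6 months only. The inclusion criteria (Part 2, Study population) admit a patient with hypertension on either of two grounds: uncontrolled pressure, or non-adherence on the Morisky scale. A patient whose pressure is already controlled can therefore enter.

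**The concern.** The outcome is named on one scale and its success is defined on another. The responder rule also fits a one-group design poorly, for three reasons.

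- A fall of more than 10% exists only once both visits are done. The composite cannot be computed at baseline, so there is no before-and-after comparison of it.
- The table sets no responder share that would count as success and no share expected without the programme. The adherence row of the same table at least has a group-level threshold, a 10% shift. The blood pressure row has none.
- The at-target limb looks only at the final visit. A patient who enters at target and stays there is counted as improved, even if pressure has risen.

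If the report gave the percentage improved and drew its conclusion from that, an ineffective programme could appear to have helped a large part of the patients.

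**Working it through.** The plan has no blood pressure figure to reproduce. Its sample size of 150 is derived from adherence categories. All blood pressure inputs below are assumptions.

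**Inputs.** n = 150 and two-sided 0.05 (150 and 0.05 are from the article; two-sided is assumed). Mean SBP 140, 148 or 155 mmHg; SD 18 or 22; correlation r between visits 0.5 or 0.7; half of the pool non-adherent; 10% on the lower target. Screening, baseline and 6-month readings were simulated, applying the article's entry rule at screening and the Table 2 rule at 6 months. A rerun with diastolic SD 11 when systolic SD is 18 (scaled with it) and systolic-diastolic correlation 0.6 agreed to within one percentage point.

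**Step 1: one limb by hand.** Without a true change, SBP falls by more than 10% when final − 0.9 × baseline is below zero. In an unselected population with mean 148, SD 18 and r = 0.5, that quantity has mean 0.1 × 148 = 14.8 and SD 18 × √(1 + 0.81 − 1.8 × 0.5) = 17.17. The probability is Φ(−14.8/17.17) = Φ(−0.862) = 19%. With r = 0.7 the SD is 18 × √(1.81 − 1.26) = 13.35 and the probability is Φ(−1.109) = 13%. So one of the three ways of meeting the rule already yields 13% to 19% by ordinary variation.

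**Step 2: the whole rule.** Share meeting Table 2 with no true change, then with a true fall of 5 mmHg systolic and 3 mmHg diastolic:

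| SD, r | Mean SBP 140 | Mean SBP 148 | Mean SBP 155 |
|---|---|---|---|
| 18, 0.5 | 48.3% → 61.3% | 38.1% → 51.1% | 31.7% → 44.1% |
| 18, 0.7 | 43.0% → 57.7% | 31.8% → 46.5% | 24.5% → 38.6% |
| 22, 0.5 | 50.9% → 61.7% | 43.0% → 53.9% | 37.7% → 48.5% |
| 22, 0.7 | 45.9% → 58.4% | 37.0% → 49.7% | 31.0% → 43.6% |

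The no-effect rates span 24.5% to 50.9% and the rates with a real fall span 38.6% to 61.7%. An observed share between about 39% and 51% fits either.

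**Step 3: who is counted, with no true change.** Of patients at target at baseline, 33% to 65% are classed as improved. Of all patients classed as improved, 15% to 29% have a higher SBP than at baseline. A simpler simulation without the entry rule (SBP 148, SD 18; DBP 90, SD 11; the 140/90 target only) gives about 36% to 41% meeting the rule, and 22% to 25% of those with a higher SBP.

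**Step 4: guessing the reference rate.** Approximate power of a one-sample test is Φ[(|p − p0|√n − 1.96√(p0(1 − p0)))/√(p(1 − p))]. If the true no-effect rate is p = 0.381 and the test uses p0 = 0.30, this is (0.081 × 12.247 − 1.96 × 0.458)/0.486 = 0.19, so a programme with no effect is declared effective 58% of the time. With p0 = 0.25 it is 94%.

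**Step 5: is power the problem?** At a 5/3 mmHg fall, the paired t-test on SBP has 79% to 99% power. With SD of change 18, for example, 5/18 × 12.247 = 3.40, giving about 92%. The composite tested against a known no-effect rate has 76% to 97%. For p0 = 0.381 and p = 0.511: (0.130 × 12.247 − 1.96 × 0.486)/0.500 = 1.28, giving 90%. A McNemar test on at-target status at the two visits has 39% to 77%. The composite loses little power if its reference rate is known. What it lacks is that rate.

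**The case against.** The strongest reply is that Table 2 is never called the analysis variable. It can be read as a benchmark for a worthwhile change in one patient, while the named outcomes, SBP and DBP, can be computed at both visits exactly as Statistical methods says. The choice of test and the role of responder shares may sit in a fuller plan that is not shown. This stands in part. A reader might infer that the article replaces the mmHg changes with the responder class, or that its blood pressure outcome cannot be tested at all, but the article says neither. The named changes can be tested, and the at-target limb alone has a baseline value.

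A reader might also infer that dichotomising costs much power here. That holds only for a McNemar test on at-target status, which the article does not propose.

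A reference might come from elsewhere: in the Discussion the authors write "we consider analyzing the data collected during QUICK - I study for the patients included in QUICK - II". Such data could yield a pre-programme responder rate. The idea is only under consideration, however, and no rate or method is fixed.

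Finally, mean change without a control group cannot separate the programme from time trends or other care either. The Discussion concedes that the design "could have been improved by using a control group and a randomized design". Changing the scale does not cure this.

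What survives is that the only success criterion printed for blood pressure is one that, reported alone, has nothing to be compared with. This is set out in the article's own table and is not a detail left for later.

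**Conclusion.** The point holds as a mismatch between the named outcome and its success definition. A responder percentage from Table 2 cannot by itself support a conclusion on blood pressure, because 25% to 51% of patients would meet the rule with no true change and 15% to 29% of those would have a higher SBP than at baseline. These ranges rest wholly on assumed means, SDs, correlations and case mix. That the composite has no baseline value, and that the article gives no reference rate, follows from the text and needs no assumption. Blood pressure is a secondary outcome and the sample size does not depend on it, so this should be corrected but does not threaten the primary analysis.

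**What to change.** State in Table 2 and in Statistical methods that the conclusion on blood pressure rests on mean paired change in SBP and in DBP (mmHg) from baseline to 6 months, each with a 95% confidence interval. Keep the Table 2 classification, and the share at target at each visit, as descriptive results. The target levels need not change.

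Add a sentence that paired mean change still carries two limits: the absence of a control group, and regression to the mean, since some patients are selected for raised pressure. The second matters most if the reading that qualified the patient also serves as baseline.

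The cost is wording only, with no new data or patients. The downside is that the responder percentage loses its standing as the success criterion for blood pressure.

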## Part 2: Evaluation of Chep

### Study population

To be included in the evaluation study of the effect of CHEP (part 2), patients have to meet the following inclusion criteria. They must: (i) be enrolled in HCHP; (ii) be registered as a patient in OOH; (iii) be included in the QUICK - I study for at least 12 months; (iv) have a diagnosis of hypertension; (v) have uncontrolled BP (≥140 mmHg systolic or ≥90 mmHg diastolic) or be non adherent to prescribed medication or any other recommended life style changes according to their score on the Morisky scale [14]; and (vi) be ≥18 years of age. Patients who meet these inclusion criteria will be excluded if their treating health care professional judges them unfit for participation (e.g. due to co morbidity) or if they are not capable or unwilling to give informed consent. Female patients who are pregnant or lactating will be excluded from the entire study because the etiology, prognosis and treatment regimes of gestational diabetes and pregnancy-induced hypertension are different compared to hypertension and diabetes in non-pregnant women.

To be included in the qualitative interviews for the feasibility analysis, healthcare professionals must: (i) be a HCP in OOH who participated in the implementation of CHEP, or be managers and doctors of HCHP; and (ii) give informed consent.

Table 1 shows an overview of the inclusion and exclusion criteria for CHEP study. For an overview of the inclusion and exclusion criteria of QUICK - I, see the article of the QUICK - I study design [8].

**Table 1 T1:** Inclusion and exclusion criteria for CHEP study.

Inclusion Criteria	Exclusion Criteria
Patients:	Patients:
• Enrollment in HCHP	• Unwillingness to give informed consent
• Registered and accessing care in OOH	• Unfit for participation (e.g. due to co morbidity)
• Inclusion in QUICK - I for at least 12 months	• Pregnant or lactating females
• Diagnosis of hypertension	
• Uncontrolled hypertension or non adherence to prescribed medication or lifestyle changes after 12 months in QUICK - I	
• Age of 18 years and over	
• Give informed consent	

Healthcare Professionals for interviews on feasibility of CHEP:	
• HCP of OOH who participated in the implementation of CHEP, or	
• Managers and Doctors of HCHP	
• Give informed consent	

Figure 1 describes the project populations for QUICK - II and their relationship to the QUICK - I study.

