#### Patient recruitment

The following steps will be applied in recruiting patients for the CHEP study:

1. Researchers will use the records of the QUICK - I study to identify all patients with uncontrolled hypertension or with low or medium adherence scores for medication or other life style measures on the Morisky Scale at 12 months after inclusion into the study.

2. Eligible patients will be informed about QUICK-II and invited for participation through a written invitation.

3. A research assistant will assess patients who are interested in participating for eligibility criteria and eligible patients will be asked to give informed consent.

4. Patients who give informed consent will be invited to a one-hour baseline assessment session.

5. Included patients who have completed baseline assessments will be invited to have three CHEP sessions spaced over a period of 4 months and one final assessment interview six months after baseline.

To encourage participation, all included patients will be reimbursed for extra travel costs incurred in visiting for assessments and CHEP sessions outside their normal clinic days.

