### Materials and Measurements

We will use the following measurements and materials to evaluate the effects of CHEP: patients' adherence to medication and other life style recommendations will be measured by using the five point Morisky Scale; and patients' blood pressure will be measured using pre validated OMRON M6 Comfort electronic equipment. The blood pressure will be measured on 3 occasions with the patient seated comfortably for 5 minutes, and the last two values averaged. All other physiological measures will be performed according standardized procedures using standard equipment. Other self-reporting measures (see Table 3) will be measured using the questionnaire of the OHD 2 trial in the Netherlands [16]. Aspects of this questionnaire will be adapted to the Nigerian specifics where necessary.

**Table 3 T3:** Timelines and measures used in CHEP study

Measures	Baseline	Final
Physiological measures		
- Clinic BP measurements, Heart rate	X	X
- Height, weight, Body Mass Index	X	X
- Hip and waist circumference	X	X

Self-reporting measures		
- Patient demographics	X	
- Additional cardiovascular risk factors (physical activity, diet, smoking, alcohol, sodium intake)	X	X
- Medication adherence	X	X
- Adherence to lifestyle recommendations	X X	X X
- Knowledge of HTN	X	X
- Perceptions of HTN	X	X
- Perceptions of medication	X	X
- Self efficacy	X	X
- Satisfaction with care	X	X
- Perception of stress	X	X

Case file data		
- Prescribed medication	X	X
- Prescribed lifestyle measures	X	X
- Co-morbidity	X	X

Process data		
- Records office visits, patient drop-out data etc	X	X
- HCP interviews		X

All assessments will take place at baseline and 6 months after. A trained nurse will perform all physiological assessments. A trained interviewer will perform pre- and post CHEP assessment interviews. The researcher will be responsible for the training of the nurses and the interviewers.

Table 3 presents all the measurements that will be used in the study.

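### Table 2's blood pressure label counts movement one way only, and for many patients its target line mirrors the entry cut-off, so some 'improvement' is expected with no programme effect

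*Protocol article*

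**What the plan says.** All places are in Part 2 of the protocol article.

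- **Entry (Study population, criterion v).** Blood pressure is one of two ways in: "have uncontrolled BP (≥140 mmHg systolic or ≥90 mmHg diastolic) or be non adherent to prescribed medication" (or to lifestyle advice).
- **Selection (Patient recruitment, step 1).** Researchers use the QUICK-I records at 12 months to "identify all patients with uncontrolled hypertension or with low or medium adherence scores". Step 3 has an assistant assess eligibility again, without saying whether blood pressure is re-measured for it.
- **Success (Outcomes, Table 2).** Two routes joined by 'or': "Blood pressure decrease of >10% systolic or diastolic or blood pressure at target level". The target route is spelled out as "blood pressure at target level (patients without diabetes or established CVD: <140 mmHg systolic and <90 mmHg diastolic". A stricter line applies to others: "patients with diabetes, renal disease or established CVD: <130 mm Hg systolic and <80 mmHg diastolic".
- **Measurement (Materials and Measurements).** "The blood pressure will be measured on 3 occasions with the patient seated comfortably for 5 minutes, and the last two values averaged". "All assessments will take place at baseline and 6 months after". No confirming visit is described.
- **Design (Discussion).** There is no control group. A comparison with the same patients' QUICK-I data is something the authors consider, not a commitment.
- **Listed outcomes.** Changes in systolic and diastolic pressure at six months are secondary outcomes. Adherence is primary.

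**The concern.** Patients picked because a reading lay above a line will, on re-measurement, sometimes lie below it even if nothing has changed. This is regression to the mean plus ordinary visit-to-visit variation. Averaging two readings within a session does not remove variation between visits. Table 2 scores the downward crossing as success and has nothing to offset patients who move up. As worded, the target route does not even require a patient to be above target at the baseline session. Someone who was selected on the QUICK-I record, or who entered through non-adherence, and who is already at target at baseline counts as improved simply by staying there.

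Without a control group, the share of such successes cannot be observed directly. If the percentage meeting Table 2 is reported as a result of CHEP, an unknown part of it is an artefact of selection and noise.

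**Working it through.** **1. Compare the two lines.** Entry on blood pressure: systolic ≥140 or diastolic ≥90. Target without diabetes, renal disease or established CVD: systolic <140 and diastolic <90. The second is the exact logical complement of the first. Because the target route is joined by 'or' to the >10% fall, it carries no minimum change. A move from 140/85 to 139/85 qualifies, a fall of 1/140 = 0.7%.

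**2. Inputs for the size.** The cut-offs and the >10% rule come from the article. It gives no blood pressure means or variability, so the rest is assumed: mean 145/90, between-patient SD 15/9, visit-to-visit SD 5/3 to 12/7, systolic-diastolic correlation 0.6, selection on one earlier reading, no true change.

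**3. Model.** True pressure T is bivariate normal. The reading at visit v is X_v = T + e_v, with independent visit errors (0 = QUICK-I record, 1 = baseline session, 2 = six months).
- S (selected): X_0 ≥140 systolic or ≥90 diastolic.
- A (at target): X_2 <140 systolic and <90 diastolic.
- D (fall >10%): X_2 < 0.9 × X_0, systolic or diastolic.

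The label is A or D, so P(label | S) = P(D | S) + P(A without D | S). Simulation, 1,000,000 patients per setting, qualifying reading as baseline:

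| Visit SD | At target (A) | Target line alone (A without D) | >10% fall (D) | Either (sum of the last two) |
|---|---|---|---|---|
| 5/3 | 9.0% | 7.5% | 2.9% | 10.4% |
| 8/5 | 13.6% | 6.4% | 16.8% | 23.2% |
| 10/6 | 16.0% | 5.3% | 24.9% | 30.2% |
| 12/7 | 18.1% | 4.4% | 32.1% | 36.5% |

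The target line's own contribution shrinks as noise grows, because more of the crossings also meet the >10% rule (at 12/7, 18.1 − 4.4 = 13.7 points of the 18.1). From visit SD 8/5 upward the >10% route is the larger source.

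**4. Sensitivity.**
- Mean pressure: with a mean of 140/86, 13% to 25% are at target with no effect; with 155/94, 4% to 10%.
- Baseline: if patients are also uncontrolled at the baseline session and that reading is the baseline (mean 145/90), 5% to 13% are at target and 7% to 33% meet either route.
- Distance from the line: a patient with true pressure 140/85 reads at target 46% to 50% of the time; one with true pressure 150/90, 2% to 17%.

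**5. Check of the remedy.** If selection uses only X_0, then X_1 and X_2 have the same distribution given S, so P(at target at X_2 | S) − P(at target at X_1 | S) = 0 with no effect. The same holds for the mean change from X_1 to X_2. It fails if X_1 is itself used to select patients.

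**The case against.** The strongest reply has four parts.

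- **It is a label on a secondary outcome.** The study is powered on adherence, and changes in systolic and diastolic pressure are already listed and calculated for every patient. This stands, and it limits the point to how the Table 2 percentage is used.
- **Defining controlled as the opposite of uncontrolled is ordinary practice.** Also true. A reader might infer that the matching cut-offs are an error in themselves, or that the 9% to 18% at target is the damage done by that line. Neither follows: the line alone adds about 4% to 8%, and at moderate or high visit variability the >10% route adds more.
- **The selection details are partly unknown.** The article does not say that one single value qualifies a patient; how QUICK-I classified control is described elsewhere. If pressure is rechecked before baseline, the lower figures in step 4 are nearer the mark.
- **The missing control group is acknowledged.** It is, but the Discussion gives contamination and feasibility as the reasons. The QUICK-I comparison is tentative and leaves Table 2 unchanged.

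A reader might also infer that noise explains most blood pressure successes, or that all patients are affected alike. The article does not support this. Chance crossings concern a minority, mainly near 140/90, and patients with diabetes, renal disease or established CVD face a target stricter than the entry line.

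**Conclusion.** The point holds as a limit on what the Table 2 blood pressure percentage can show. For patients without diabetes, renal disease or established CVD who enter on blood pressure, the target line mirrors the entry line without a minimum fall. Both routes to the label count one direction only, in a design that cannot show the no-effect rate directly.

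The direction of the bias follows from the wording; the size rests on the assumptions in step 2. At a mean of 145/90, about 10% to 37% of patients uncontrolled at selection would earn the label with no effect, or 7% to 33% if they are also uncontrolled at a baseline session that serves as the baseline. The primary adherence outcome is untouched by this point. It should be corrected before results are reported.

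**What to change.** 1. State that the percentage of patients meeting Table 2, by either route, is not evidence that CHEP lowers blood pressure. Keep the label, if at all, as descriptive. No new mmHg threshold is needed.
2. Base the blood pressure conclusion on two quantities in all enrolled patients:
   - the already listed mean change in systolic and diastolic pressure from the baseline session to six months;
   - the paired change in the proportion at target between those two sessions, counting crossings in both directions, as a McNemar-type estimate with a 95% confidence interval.
3. Use the baseline-session reading as the starting value, not the QUICK-I record used for selection, and state that blood pressure at the baseline session does not decide eligibility. If it does, the zero expected net change no longer holds, and that should be said.

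This removes the bias from selection and one-way counting. It does not replace a control group, so other changes over the six months remain mixed with the programme effect.

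Cost: wording in Table 2 and in Statistical methods. No extra visits or measurements are needed. The downside is a less favourable reported blood pressure success percentage.

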**Methods/Design:**

*Design: *The study has two parts. Part *1 *will develop a cardiovascular health education program, using qualitative interviews with stakeholders. Part *2 *will evaluate the effectiveness of the program in patients, using a prospective (pre-post) observational design.

*Setting: *A rural primary health center in Kwara State, Nigeria.

*Population: *For part 1: 40 patients, 10 healthcare professionals, and 5 insurance managers. For part 2: 150 patients with uncontrolled hypertension or other cardiovascular risk factors after one year of treatment.

*Intervention: *Part *2*: patient-centered cardiovascular health education program.

*Measurements: *Part 1: Semi-structured interviews to identify stakeholder perspectives. Part 2: Pre- and post-intervention assessments including patients' demographic and socioeconomic data, blood pressure, body mass index and self-reporting measures on medication adherence and perception of care. Feasibility of the intervention will be measured using process data.

*Outcomes: *For program development (part 1): overview of healthcare professionals' perceptions on barriers and facilitators to care, protocol for patient education, and protocol implementation plan.

For program evaluation (part 2): changes in patients' scores on adherence to medication and life style changes, blood pressure, and other physiological and self-reporting measures at six months past baseline.

*Analysis: *Part 1: content analytic technique utilizing MAXQDA software. Part 2: univariate and multilevel analysis to assess outcomes of intervention.

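### Table 2 counts any fall in BMI as improvement, so with no true change about half of patients with BMI above 25 would qualify

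*Protocol article*

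**What the plan says.** The Outcomes section of Part 2 lists changes in physiological measures as secondary outcomes, among them "body mass index (BMI) or abdominal obesity at 6 months after baseline". It introduces Table 2 with: "Table 2 indicates definitions of what we consider as significant improvement per outcome measure". The BMI row gives three risk bands and then the rule: "In patients with a BMI >25 any reduction of BMI at 6 months will be regarded as an improvement". The blood pressure row of the same table asks for more: "Blood pressure decrease of >10% systolic or diastolic or blood pressure at target level".

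Materials and Measurements states: "All assessments will take place at baseline and 6 months after". Repeated readings with averaging are described for blood pressure only. For the rest it says: "All other physiological measures will be performed according standardized procedures using standard equipment". The abstract describes Part 2 as "using a prospective (pre-post) observational design", and the Discussion concedes: "The design of our evaluation of CHEP could have been improved by using a control group and a randomized design". Comparison with QUICK-I data on the same patients is mentioned there only as something under consideration.

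**The concern.** A rule that accepts a fall of any size responds to the sign of the difference between two measurements. Weight fluctuates and measurement has error, so two BMI values taken six months apart will seldom be identical. If nothing has changed, some patients go down and a similar number go up, and the rule labels those who go down as improved.

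The plan fixes no control arm or other comparison that would show what share to expect without the programme. A report that half of the overweight patients improved could then be read as a benefit of the programme, although it is roughly what no effect would produce. The rule is stated in the current text, so this is not a detail left to a fuller document.

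**Working it through.** The article gives no expected BMI change, SD or responder rate, so there is no BMI figure of its own to reproduce. The inputs from the article are the rule (change below 0, baseline BMI above 25), two time points and no control arm. All SDs, BMI distributions, drifts and counts below are assumptions.

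**1. No true change, no drift, no selection.** Let D be follow-up minus baseline BMI, each value carrying independent symmetric error with SD s. D is then symmetric about 0, so P(D < 0) = 0.5 whatever the value of s.

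**2. Selection on observed BMI above 25, and rounding.** Simulation of 2,000,000 patients per case, with true BMI normal (mean 25 or 27, SD 3 or 5) and no drift:

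| Within-person SD (kg/m²) | Any fall, unrounded | Any fall, BMI rounded to 0.1 (ties not counted) |
|---|---|---|
| 0.2 | 50.6-51.4% | 43.6-44.5% |
| 0.4 | 51.3-53.0% | 47.8-49.5% |
| 0.6 | 52.0-54.4% | 49.6-52.1% |
| 1.0 | 53.1-57.2% | 51.7-55.9% |

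The overall range is 43.6-57.2%. The unrounded rates exceed 50% because patients are selected on an observed baseline, which brings regression to the mean. The same selection produces an apparent mean fall of 0.004 to 0.25 kg/m² when nothing has changed. The largest value can be checked by hand. With true mean 25, true SD 3 and s = 1.0, the observed variance is 9 + 1 = 10 and the SD 3.162. The mean excess over 25 among those selected is 0.798 × 3.162 = 2.52, and the expected fall is (1/10) × 2.52 = 0.25.

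**3. With drift.** Ignoring selection, P(D < 0) = Φ(−mean/SD of D). A mean gain of 0.1 with SD of change 1.0 gives Φ(−0.10) = 0.46. A mean gain of 0.2 with SD 0.6 gives Φ(−0.33) = 0.37. So 37-46% would still be classed as improved while the group gained weight. In the simulation, a net rise of 0.3 kg/m² gives about 11-49% improved and a net fall of 0.3 gives about 60-86%.

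**4. Chance spread.** If 75 patients had BMI above 25, the expected number improved at a rate of 0.5 is 37.5. The upper limit of the one-sided 97.5% range is 46, and 46/75 = 61%.

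**5. Effect of a minimum fall (illustration only).** With no true change, requiring a fall of at least 5% would class about 0% as improved at s = 0.2, 0.6-1% at 0.4, 4-6% at 0.6 and 16-21% at 1.0.

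**The case against.** The strongest reply is that the outcome is already named as a change in BMI, and an analysis of mean change would not have this fault. On that view Table 2 only adds a label. No sentence says that a percentage of BMI improvers will be tested or used to declare success. The BMI cell says improvement, and the word significant comes from the table's title, column head and introduction. The adherence row is a group-level criterion, so the BMI row could also be meant for the group. The lack of a comparator is openly acknowledged.

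Most of this stands and limits the weight of the point. It does not repair the rule. The row is the only BMI improvement criterion in the article. The per-patient reading is the more natural one, because the row speaks of patients with BMI above 25 and Statistical methods has outcomes calculated for every patient at both times. The group reading cannot be excluded; under it the criterion would be the sign of a mean change, again without a minimum size.

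A reader might infer that about half of the overweight patients will be counted as successes whatever happens. The documents do not support that, since the figure requires zero net weight drift and step 3 shows how far it moves otherwise. A reader might also think that testing the share against 50% would settle the matter. In patients selected on observed BMI above 25, the no-effect rate for unrounded values is 50.6-57.2%, so such a test leans towards benefit.

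**Conclusion.** The point holds in a limited form. Read per patient, the BMI rule cannot separate benefit from no effect. With no true change and no net drift, about 44-57% of patients with baseline BMI above 25 would be classed as improved. The value of one half rests on symmetry alone; the range rests on the assumed within-person SDs of 0.2-1.0 kg/m², the assumed BMI distributions and the rounding. In a single-arm study the share improved is therefore not evidence of effect by itself.

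The point concerns a secondary outcome. It does not touch the adherence outcome or the sample size of 150, and the article ties no success decision to the BMI share. It is worth correcting, but it does not undermine the study.

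**What to change.** Replace the improvement rule in the BMI row of Table 2 with mean change in BMI from baseline to 6 months, with a 95% CI, in all patients. Using all patients avoids the regression to the mean that comes from selecting on baseline BMI. Give the same estimate for patients with baseline BMI above 25 as a supporting result, and note that selection on the observed baseline produces a small apparent fall.

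If a responder figure is kept, define it by a minimum percentage fall fixed in advance, show the share with an equal-sized rise beside it, and do not present the share as evidence of effect. Do not test it against 50% in the subset with BMI above 25. A threshold tied to repeat-measurement error would need data that the article does not describe collecting, so a fixed percentage is simpler.

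The cost is one reworded table row. Height and weight are already measured at both visits (Table 3). The reported success rate will be lower, and the all-patient mean will include patients for whom Table 2 sets no BMI improvement. The change does not supply a comparator: a weight trend unrelated to the programme would still appear in the mean change.
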